#### Revised Child Anxiety and Depression Scale-30

The Revised Child Anxiety and Depression Scale-30 (RCADS-30) [32] is a widely-used questionnaire measuring self-reported anxiety and depressive symptoms in children and adolescents. The scale is comprised of the following subscales derived from the Diagnostic and Statistical Manual of Mental Disorders, 4th edition (DSM-IV) criteria: (1) social phobia, (2) generalized anxiety disorder, (3) obsessive-compulsive disorder, (4) panic disorder, (5) separation anxiety disorder, and (6) major depressive disorder. The 6 subscales are summed to create a Total Anxiety and Depression score. Each item is scored from 0 (“Never”) to 3 (“Always”), with higher scores representing more severe symptoms. The RCADS-30 has demonstrated good psychometric properties with normative and clinical populations [33,34]. In the current sample, the 6 individual subscales have demonstrated adequate to good internal consistency both at Time 1 (alpha .70 to .85) and at Time 2 (alpha .72 to .86). The Total Anxiety and Depression scale has demonstrated excellent internal consistency at Time 1 (alpha = .92) and at Time 2 (alpha = .93) assessments.

#### Depression Questionnaire for Children

Depression Questionnaire for Children (Cuestionario de Depresión para Niños; CDN) [35] is a 16-item, self-report questionnaire designed to assess symptoms of DSM-IV major depressive disorder and dysthymic disorder in children and adolescents. In this study, the 2 items targeting suicidal ideation were not included as per the request of school personnel. Participants rate each item on a 3-point scale from 0 (“Never”), 1 (“Sometimes”), to 2 (“Very often”) to indicate the frequency with which they experience depression symptoms. The sum of all items provides an overall score, with higher scores indicating greater depression symptoms. The CDN has demonstrated adequate psychometric properties [32]. At Time 1 and Time 2 assessments, the CDN overall scale has demonstrated good internal consistency in this sample with alpha values of .87 and .89, respectively.

#### Anxiety Scale for Children

Anxiety Scale for Children (Escala de Ansiedad para Niños; EAN) [35] is a 10-item questionnaire that assesses anxiety symptoms during the past few weeks in children and adolescents. Participants are instructed to indicate how frequently they have experienced general anxiety symptoms on a 4-point, Likert-type scale, ranging from 0 (“Never or almost never”) to 3 (“A lot of the times or almost always”). The sum of all items provides an overall score, with higher scores indicating more elevated anxiety symptoms. The EAN has shown good psychometric properties [36]. In the current sample, the EAN scale has demonstrated excellent internal consistency at Time 1 (alpha = .91) and Time 2 (alpha = .94) assessments.

### Secondary Outcome Measures

The following questionnaires will be completed at Time 1, Time 2, Time 3, and Time 4 assessments (see Table 2).

#### Top Problems Assessment

The adolescent version of TPA provides a means of collecting information about changes in the severity of problems identified by the adolescent to be of greatest concern. Group leaders first provide instructions and examples about the types of problems that can be targeted within the program and adolescents are then asked to generate 3 top problems of their own. Adolescents also generate a corresponding specific, measurable, attainable, relevant, and time-bound (SMART) goal for each problem. During the 1st, 5th, and 9th sessions, participants are asked to rate the severity of each problem on a 0 to 8 scale (with higher ratings indicating greater problem severity). Top problems are a central tool for progress monitoring in the UP-A and UP-C protocols. They were adapted by [name] from original work by Weisz and colleagues [37]. Top problems have been shown to demonstrate good psychometric properties [37].

#### Strengths and Difficulties Questionnaire

The Spanish version of the Strengths and Difficulties Questionnaire (SDQ) by García and colleagues was used [38,39]. The scale provides scores for 5 subscales including emotional symptoms, conduct problems, symptoms of hyperactivity/ inattention, peer problems, and prosocial behavior. Each subscale contains 5 items scored on a 3-point, Likert-type scale, ranging from 0 (“Not true”) to 2 (“Certainly true”). A Total Difficulties Score is obtained by summing the 5 items on all scales, with the exception of the prosocial behavior scale. The SDQ is widely used and both the original and Spanish versions have good psychometric properties [40,41]. The Total Difficulties Scale has demonstrated adequate to good internal consistency in this sample at Time 1 (alpha = .73) and Time 2 (alpha = .81) assessments.

#### Depression and Anxiety Interference Scale for Children

Students complete a Depression and Anxiety Interference Scale for Children (Escala de Interferencia de la Depresión y Ansiedad para Niños; EIDAN) [42] developed for this investigation. This 11-item questionnaire assesses the degree to which feeling worried, nervous, or sad interferes with various domains of the adolescent’s life (school, peer/family/general functioning), employing a 4-point, Likert-type scale ranging from 0 (“Nothing or almost nothing”) to 3 (“A lot”). Higher scores indicate greater levels of interference. In the current sample, the EIDAN scale has demonstrated good internal consistency at Time 1 (alpha = .80) and Time 2 (alpha = .87) assessments.

#### Positive and Negative Affect Schedule for Children and Adolescents

The Positive and Negative Affect Schedule for Children and Adolescents (Escalas PANAS de Afecto Positivo y Negativo para Niños y Adolescentes; PANASN) [43] questionnaire is an age-downward version of the Positive and Negative Affect Schedule [44] for individuals aged 7 to 17 years. The scale provides scores for 2 subscales of 10 items each measuring positive and negative affect. Participants are asked to rate items according to how they usually feel from 1 (“Never or almost never”), 2 (“Sometimes”), to 3 (“A lot of the time”). The PANASN has demonstrated good psychometric properties [43,45]. In the current sample, the Positive Affect Scale demonstrated adequate and good psychometric properties at Time 1 (alpha = .77) and Time 2 (alpha =.81) assessments. Similarly, the Negative Affect Scale demonstrated adequate internal consistency at Time 1 assessment (alpha = .79) and good internal consistency at Time 2 assessment (alpha = .81).

#### Childhood Anxiety Sensitivity Index

The Spanish version of the Childhood Anxiety Sensitivity Index (CASI) [46,47] was used for this study. The CASI is an 18-item self-report questionnaire measuring anxiety sensitivity in children or distress reactions to symptoms of anxiety (eg, “It scares me when my heart beats fast”). Participants rate the frequency with which they experience each item using a 3-point, Likert-type scale from 1 (“Never”), 2 (“Sometimes”), to 3 (“A lot of the time”). The Spanish adaptation of the CASI used in the present study has demonstrated good psychometric properties and positive correlations with constructs related to anxiety sensitivity [48]. In the current sample, the CASI has demonstrated excellent internal consistency at Time 1 (alpha = .90) and Time 2 (alpha = .90) assessments.

#### Emotional Avoidance Strategy Inventory for Adolescents

Emotional Avoidance Strategy Inventory for Adolescents (EASI-A) [49] is a 17-item self-report questionnaire in which respondents are instructed to indicate the degree to which each statement is true using a 5-point, Likert-type scale ranging from 0 (“Not at all true of me”) to 4 (“Extremely true of me”). The EASI-A was translated and adapted to Spanish for this study [50]. Our Spanish adaptation also uses a 5-point Likert-type scale, but with options indicating frequency rather than degree from 0 (“Never or almost never”), 1 (“Seldom”), 2 (“Sometimes”), 3 (“A lot of times”), to 4 (“Always or almost always”). The EASI-A has demonstrated good psychometric properties and positive correlations with anxiety and depression symptoms [49]. The EASI scale has demonstrated good internal consistency at Time 1 and Time 2 assessments with alpha values of .87. and .86, respectively, in the current sample.

#### Satisfaction with Life Scale for Children

The Satisfaction with Life Scale for Children (SWLS-C) [51] measure is an age-downward version of the measure of life satisfaction developed by Diener and colleagues [52]. It is a 5-item, self-report instrument in which respondents are asked to indicate the degree to which each statement is true of their life using a 4-point, Likert-type scale ranging from 1 (“Not at all”) to 4 (“A lot or completely”). In the current sample, the SWLS scale has demonstrated adequate good consistency at Time 1 (alpha = .81) and Time 2 (alpha = .89) assessments.

#### Kidscreen-10

The official Spanish version developed by the KIDSCREEN Group was used [53]. KIDSCREEN-10 is a widely-used brief questionnaire assessing generic health-related quality of life in children and adolescents that was adapted from the longer KIDSCREEN-27 [53]. The 10 items on the KIDSCREEN-10 index assess affective symptoms of depressed mood, difficulty concentrating, decreased energy, impaired school functioning, and impaired relations with peers and family. It uses a 5-point, Likert-type scale ranging from 1 (“Not at all”) to 5 (“Extremely”). KIDSCREEN-10 has been shown to possess good psychometric properties [54]. In the current sample, the KIDSCREEN-10 scale has demonstrated good internal consistency at Time 1 (alpha =.82) and Time 2 (alpha = .85) assessments.

#### Self-Esteem Scale

A Spanish adaptation of the Self-Esteem Scale (SES) [55] was used in this study [56]. SES is a 10-item self-report instrument that measures global self-esteem. Respondents are asked to indicate how much they agree with each statement on a 4-point, Likert-type scale from 1 (“Strongly disagree”) to 4 (“Strongly agree”). The scale has been shown to possess good psychometric properties in adolescent samples [57]. In the current sample, the SES scale has demonstrated good internal consistency at Time 1 (alpha = .83) and excellent internal consistency at Time 2 (alpha = .90) assessments.

#### School Adjustment Brief Scale

School Adjustment Brief Scale (Escala Breve de Ajuste escolar; EBAE-10) [58] is a 10-item questionnaire used to measure adaptive functioning in the area of school performance. Respondents are instructed to respond to questions about their grades, their relationships with teachers and peers, and their expectations regarding their educational future. They are asked to indicate how much they agree with each statement on a 6-point, Likert-type scale ranging from 1 (“Completely agree”) to 6 (“Completely disagree”). This scale has demonstrated adequate psychometric properties [59]. In the current sample, the EBAE scale has demonstrated acceptable internal consistency at Time 1 (alpha=.76) and Time 2 (alpha=.72) assessments.

#### General Indiscipline Scale

The General Indiscipline Scale (Escala de Indisciplina General; IG), adapted from Martín and colleagues’ questionnaire [60], is an 11-item questionnaire that assesses problematic behaviors of students in the classroom. Respondents are asked to indicate the frequency of each behavior stated in the items on a 4-circle bull's-eye, with each circle closer to the bulls-eye's center representing more frequent demonstration of the behavior. For this study, we adapted the scale such that adolescents were asked to rate the frequency with which they demonstrated each behavior on a 4-point, Likert-type scale with options being 0 (“Never or almost never”), 1 (“Only sometimes”), 2 (“Quite a few times”), or 3 (“A lot of the time”). The IG has demonstrated adequate properties [61]. In the current sample, this scale has demonstrated adequate internal consistency at Time 1 (alpha = .75) and good internal consistency at Time 2 (alpha= .80) assessments.

#### Socio-Demographic Information Questionnaire

All participants are asked to provide demographic information including their age, gender, school grades, socio-economic status, and place of birth.

### Other Secondary Outcome Measures

#### The Personality Inventory for DSM-5-Brief Form

The Spanish version of the Personality Inventory for Diagnostic and Statistical Manual of Mental Disorders, 5th edition-Brief Form (PID-5-BF) [62,63] was used. It assesses 5 personality trait domains (negative affect, detachment, antagonism, disinhibition, and psychoticism), with each trait domain consisting of 5 items to be rated on a 4-point scale from 0 (“Very false or often false”), 1 (“Sometimes or somewhat false”), 2 (“Sometimes or somewhat true”), to 3 (“Very true or often true”). All items are summed to derive an overall score, with higher scores indicating greater overall personality dysfunction. Similarly, higher scores in each trait domain indicate greater dysfunction in that personality trait domain. In the current sample, the PID-5-BF overall scale has demonstrated excellent internal consistency (alpha = .90).

#### Therapy and Psychology Questions

At Time 2, Time 3, and Time 4 assessments, students are also asked whether they have attended therapy in the last 3 months (and if yes, for how many sessions), as well as a question regarding their interest in psychology, rated on a 4-point, Likert-type scale from 1 (“None”) to 4 (“A lot”).

### Measures Completed at Post-Intervention Only

The following questionnaires are to be completed by students in the preventive intervention group at Time 2 and by students in the WL control group at Time 4 (Table 2).

#### Satisfaction with the Program Questionnaire

We used 6 of the 7 questions from Rapee and colleagues’ Satisfaction Questionnaire [64]. The 6 questions assess enjoyment of the program, amount learnt in the program, the effectiveness of the program in improving general life coping skills, likelihood of recommending the program to others, and the ability to cope with emotions before and after the program. We added one other question “Did this program help you to learn more about emotions and how they work?” All items are assessed on a 10-point scale from 1 (“Least or none”) to 10 (“A lot”), with the exception of questions related to recommending the program to others and whether this program increased knowledge about emotions and how they work. These latter 2 questions are assessed using a dichotomous, 2-point scale with 1 being “Yes” and 2 being “No.” Rapee and colleagues’ Satisfaction Questionnaire has showed adequate psychometric properties [24,64].

#### Discipline Problems During Sessions Questionnaire

Students are asked 6 questions about how often they demonstrated certain behaviors during the sessions using a 4-point, Likert-type scale from 1 (“In no or almost no sessions of the program“), 2 (“Only in some sessions of the program”), 3 (“In quite a lot of the sessions of the program”), to 4 (“In all or almost all sessions of the program”). Specifically, the items were (1) “I have talked to my classmates when I should not have”; (2) “I have paid attention to what the girls delivering the program were saying”; (3) “I have done things from other subjects during program sessions”; (4) “I have been reprimanded for my behavior”; (5) “I have taken the program seriously”; and (6) “I have tried to do my best when doing the in-class activities of the program.” In the current sample, this questionnaire has demonstrated only fair internal consistency at Time 2 assessment (alpha = .68).

#### Other End of Program Questions

Adolescents are also asked the following other questions related to the program: (1) “What did you like best about the program?”; (2) “What did you like worst?”; (3) “Being honest with yourself, are you going to make efforts in the future to apply the strategies that you learned in this program in your daily life?”; (4) “When you missed a session, did you read the summary of the session that was given to you?”; and (5) “When you missed a session, did you do the homework that was given to you?” Questions 1 and 2 are open-choice questions and question 3 is to be answered using a dichotomous scale with 1 being “Probably yes” and 2 being “Probably not.” Questions 4 and 5 are to be rated on a 3-point scale from 1 (”Most of the time yes”), 2 (“Most of the times no”), to 3 (“I did not miss any sessions”).

### Measures Completed at Post-Intervention and Follow-Up

The following questionnaires are to be completed by students in the preventive intervention group at Time 2 and Time 3 and by students in the WL control group at Time 4 (Table 2).

#### Curriculum Knowledge Questionnaire

A questionnaire was created on the basis of the program curriculum to assess participants’ knowledge of core information presented in the program. Specifically, there are 2 open-choice questions (“What are the three parts of an emotion?” and “What can you do when you are feeling sad or down to feel better?”) and one multiple choice question (“What is a thinking trap?”) with 3 answer choices (“It is a kind of unpleasant emotion”/“It is what happens when someone tries to trick us into thinking what they want”/“It is a thought that makes us feel unpleasant emotions”).

#### Strategies Practiced Outside of Session Questionnaire

We adapted the questionnaire for our study based on the format used in a previous study by Johnson and colleagues [65]. Students are asked “During the 9-week course, how often did you practice each of the following techniques outside of the lessons?”, are supplied with a list of techniques learned during the course, and are asked to rate how much they practiced each technique. Adolescents rate each item on a 5-point, Likert-type scale from 1 (“Never”), 2 (“Once or twice in total”), 3 (“Greater than twice in total but less than once a week”), 4 (“Once or twice each week”), to 5 (“Three times or more each week”), with higher scores indicating more frequent practice of strategies learned in the program. Specifically, participants are asked about their use of the following strategies: (1) “Identify the three parts of the emotion you are feeling (what you think, what you feel in your body and what you do)”; (2) “Plan for how long are you going to do school work and what pleasant activities are you going to do”; (3) “When you are sad or worried, do something that you like or value even if you do not feel like it”; (4) “Realize that you are falling into a thinking trap (eg, thinking the worst, ignoring the positive, etc) and try to change the thought to an alternative one that makes you feel better”; (5) “When you have a problem, think about all the possible solutions, then think about the good and bad things about each solution and, lastly, choose one of the solutions to try”; (6) “Try to focus in the present moment”; (7) “Meditate, that is, sit and try to focus in your breathing for a few minutes”; and (8) “Expose yourself little by little to those things that scare you or make you nervous because you know it is the only way to overcome your fears.” At Time 3, the question is re-worded to: “Since the end of the program at school, how often have you used the following strategies?” In the current sample, this questionnaire has demonstrated adequate internal consistency at Time 2 assessment (alpha = .82).

### Sample Size

One significant impact of the adoption of a cluster design is the comparatively large sample size requirement since, in contrast to individually randomized trials where inter-individual variation is the only source of variability, cluster studies involve both variation among individuals and variation among clusters. As a result, cluster studies must recruit a larger number of individuals in order to achieve power equivalent to that of an individually randomized trial [28]. The magnitude of this within-cluster dependence, which ultimately influences the eventual trial size, is quantified by the intracluster correlation coefficient (ICC) [66]. The ICC accounts for the extent to which responses of adolescents attending the same class (that is, sharing the same classroom, classmates, teacher, etc) are more likely to be similar compared with adolescents from a different class.

Power analyses were conducted using G*Power Version 3 software [67]. Sample size required to detect a Cohen *d* effect of .30 was estimated, based upon effect sizes reported in meta-analyses of school-based anxiety and depression preventive interventions conducted all over the world [68,69], including in Spain [70]. Calculations showed that with a power level of .80 and a significance level of alpha = .05, a total sample of N_Non-cluster_ of 74 was required to detect a significant effect. However, potential loss of power due to data clustering had to be considered in the sample size calculation. The impact of the ICC on the planned trial size depends on the so-called design effect, which can be calculated as 1+(*m*-1) ICC, with *m* referring to the number of participants recruited per cluster [66]. For this study, the ICC is unknown although, on the basis of prior school-based prevention research, the expected ICC for anxiety and depression-related outcomes is approximately 0.02 [27]. The anticipated average class (cluster) size for this study is 27 students meeting inclusion criteria, resulting in a design effect of 1.52. The design effect is then multiplied by the previously calculated N_Non-cluster_ [66], resulting in an estimated sample size for this trial of 112, considering the design effect. In addition, we estimated a dropout rate of 10% based on previous studies [65,71], resulting in an estimated total sample size of 123 (at least 62 students in each group). The total number of clusters required can be calculated dividing the estimated total sample size by the estimated number of participants recruited per cluster (123/27), resulting in 4.56 clusters [66]. Therefore, to achieve a sample of this size, a total of 157 students and 5 clusters were recruited.

As the flow diagram shows (Figure 1), the final number of participants matches these a priori computations closely: 90 students (10 lost at Time 2) were allocated to the preventive intervention group and 62 students (4 lost at Time 2) were assigned to the WL control group. In addition, this study will allow for calculation of the ICC and effect sizes for all primary and secondary outcomes, which could be very important in assisting future researchers in establishing the feasibility and ideal sample size for future full-scale cluster RCTs applying the UP-A as a preventive intervention.

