### Study Design

This study will be implemented as a 2-arm, cluster RCT [28], with an intervention condition (UP-A adapted as a preventive intervention program) and a 3-month WL control condition. Measurements will be taken on the following occasions: (1) Time 1 (1 week before the experimental group starts the intervention); (2) Time 2 (1 week after the experimental group finishes the intervention); (3) Time 3 (3 months after the experimental group finishes the intervention and 1 week before the WL control group starts the intervention); and (4) Time 4 (1 week after the WL control group finishes the intervention). On all occasions, except for Time 4, both groups will complete the outcome measures at about the same time. For Time 4, only the WL control group will complete the outcome measures. This represents a 3 (time) by 2 (group) repeated measures design. The flow diagram of the study is shown in Figure 1.

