### Limitations

This study has certain limitations due to its preliminary nature. The major limitation of this study is its moderate sample size (152 adolescents across 5 classes were randomized). In addition, the adolescents were recruited from only one school, which may limit generalizability of findings. Furthermore, due to financial and personnel constraints, this study only incorporated adolescent self-report measures. Although this methodology facilitates assessment of a large cohort of adolescents in a relatively short time frame [9], it also has limitations (eg, relies on subjective perceptions), and future studies should consider using information from multiple sources (interviews with the students, parents, and teacher reports, etc). In addition, participants were not blinded to allocation when measures were obtained due to constraints established by the Ethical Research Committee, which specified that informed consent forms must state group allocation. Lastly, using the same group leaders to administer the intervention for all classes increases consistency but, at the same time, may limit generalizability of findings [65].

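### The sample size of 74 does not give 80% power for d = .30, and five classes give roughly 17–28% power for that effect

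*Protocol article*

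**What the plan says.** All of the calculation is in the Sample Size section of the protocol article.

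- Software: "Power analyses were conducted using G*Power Version 3 software". The test, its sidedness and any within-person correlation are not named.
- Target: a Cohen d "effect of .30 was estimated, based upon effect sizes reported in meta-analyses of school-based anxiety and depression preventive interventions", "with a power level of .80 and a significance level of alpha = .05".
- Result before clustering: a total "of 74 was required to detect a significant effect".
- Clustering: expected ICC about 0.02, average class size 27, design effect 1.52, giving 112.
- Dropout of 10%, "resulting in an estimated total sample size of 123 (at least 62 students in each group"). Dividing by 27 gives 4.56, hence five classes.
- Enrolment: 90 students allocated to the intervention (10 lost at Time 2) and 62 to waitlist (4 lost). The section concludes that "the final number of participants matches these a priori computations closely".

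Study Design adds: "This represents a 3 (time) by 2 (group) repeated measures design". The Limitations section says: "The major limitation of this study is its moderate sample size (152 adolescents across 5 classes were randomized"). It does not return to the power figure.

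**The concern.** A d of .30 taken from meta-analyses of prevention programmes is naturally read as a standardised difference between arms. Detecting such a difference with 80% power takes several hundred individually randomised students, so 74 is too small by a factor of nearly five. The later steps inherit the error, and the last of them fixed the trial at five randomised units. Nothing in the chain allows for testing an arm effect on so few units.

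What is at stake is how the result is read. The Study Aims predict superiority on every outcome, and the Results section judges significance at P < .05. If the true effect is the planned one, any single test will more likely than not be non-significant. A reader who has been told that power was .80 would take that as evidence that the programme does not work. The article also offers itself as guidance for sizing future trials, so the calculation may be copied.

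**Working it through.** **Inputs from the article.** d = .30, power .80, alpha .05; 2 groups by 3 times; ICC .02; class size 27; dropout 10%; 90 and 62 allocated, so 80 and 58 at Time 2 (138 in all); five classes of about 30.

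**Assumptions not in the article.** Two-sided test; a 3 v 2 split of classes (inferred from 90 and 62 students at about 30 per class); baseline–outcome correlation of 0, .6 or .7.

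**1. Reproducing 74.** G*Power's repeated-measures within-between interaction uses λ = f²·N·m/(1 − ρ), with df 2 and 2(N − 2) when m = 3. Put f = d/2 = .15, m = 3, ρ = .5, N = 74:

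λ = .0225 × 74 × 3 / .5 = 9.99, df 2 and 144, power .806.

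N = 72 gives .795, so 74 is the first even total above .80. These settings are inferred, but they fit the 3 by 2 design.

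**2. What f = .15 means in that test.** Suppose there is no arm difference at Time 1 and a difference d at Times 2 and 3. The difference profile (0, d, d) has mean 2d/3 and deviations (−2d/3, d/3, d/3). Each arm carries half of each deviation, so the interaction variance is ¼ × (4/9 + 1/9 + 1/9)d²/3 = d²/18, and f = d/√18.

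- d = .30 gives f = .0707. Power at N = 74 is 24%, and N = 324 is needed for 80%.
- f = .15 gives d = .15 × √18 = 0.64. If the difference grows linearly over time instead, f = .15 corresponds to d = 0.73.

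**3. The direct two-arm calculation.** A two-sided two-sample t test for d = .30 needs 175.4, so 176 per arm and 352 in total (278 one-sided). With 37 per arm, power is 24.7% two-sided and 35.7% one-sided, and the d detectable with 80% power is 0.66 two-sided.

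**4. The rest of the chain.**

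| Step | As written | From 352 |
|---|---|---|
| Design effect 1 + 26 × .02 | 1.52 | 1.52 |
| N × 1.52 | 74 → 112.48 | 535 |
| Dropout | 112 × 1.10 = 123 | 535 / .90 = 594 |
| Classes (÷ 27) | 4.56 | about 22 |

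To retain 90% after dropout one divides by .90: 112.48 / .90 = 125, not 123. This is minor and still gives five classes. The right-hand column is illustrative and, like the article's own chain, makes no allowance for the number of classes.

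**5. Power of the trial as enrolled, Time 2.** With 138/5 = 27.6 students per class:

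SE = √[(.02 + .98/27.6) × (1/3 + 1/2)] = √(.0555 × .8333) = .215 SD.

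With baseline correlation r, multiply by √(1 − r²). The arm effect has 5 − 2 = 3 degrees of freedom, so the critical t is 3.18 rather than 1.96. From the noncentral t:

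| Baseline correlation | SE | Power for d = .30 | d detectable at 80% |
|---|---|---|---|
| none | .215 | 16.9% | 0.92 |
| .6 | .172 | 23.4% | 0.73 |
| .7 | .154 | 27.8% | 0.65 |

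**6. Sensitivity, Time 2, from no baseline adjustment to r = .7.**

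- 4 df, ICC .02: about 19–33%.
- 3 df, ICC .05: about 13–21%.
- Large-sample df, ICC .02: about 28–50%.
- Clustering ignored altogether, 80 v 58: 41–68%.

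**The case against.** Four points can be made for the plan.

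First, 74 is not an arithmetic slip: it is a correct software output for f = .15. That stands, and it locates the fault in the conversion from d to f. It does not rescue the statement, because the article names d = .30 and the interaction test at that d has 24% power.

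Second, the 17–28% range is conditional. The planned analysis is a complex-samples procedure and a multilevel model over three occasions, with no degrees-of-freedom rule given, and the baseline correlations are assumed. This also stands, so the range must be printed with its assumptions. The larger values come from large-sample degrees of freedom, which are anti-conservative with five classes, or from ignoring the clustering; even these stay below 80%.

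Third, the article already calls the study preliminary, names sample size as its main limitation, aims to estimate ICCs for later full-scale trials, and commits to reporting effect sizes with their precision. Much of the recommended interpretation is therefore already present. None of it withdraws the .80 claim, and the sentence on enrolment matching the calculation reinforces it.

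Fourth, recruitment and Time 2 are complete, so no estimate changes, and the chance of at least one significant result across three primary measures and two occasions is higher than for one test. Both are true. The correction concerns what the reader is told, and the power stated is for a single comparison.

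**Conclusion.** The power statement is wrong as written. For a between-arm d of .30, 74 students give about 25% power by t test and 24% by the interaction test that most plausibly produced the figure. The required totals are 352 and 324. What 74 does power is an effect about twice as large, d of roughly 0.64–0.66.

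For the trial as enrolled, power for d = .30 is about 17% unadjusted and 23–28% with baseline adjustment, and the effect detectable with 80% power is 0.92 SD and 0.65–0.73 SD respectively. These figures rest on a two-sided test at Time 2, ICC .02, a 3 v 2 split, 3 degrees of freedom and baseline correlations of .6–.7. The exact range moves with those choices, to about 13–50% for an analysis that respects the clustering. The conclusion does not move. The dropout step (123 against 125) is a minor side error.

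**What to change.** In the Sample Size section:

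- Withdraw the claim of .80 power for d = .30 and the sentence saying that enrolment matches the calculation.
- State the calculation actually used: test, f, number of measurements, assumed correlation, sidedness.
- Give the power for d = .30 with five classes (about 17–28%) and the effect detectable with 80% power (about 0.65–0.92 SD), together with the ICC, degrees of freedom and baseline correlation assumed and the wider sensitivity range.
- Correct the dropout step to 112.48 / .90 = 125.

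In the Limitations and Conclusions, say that the trial is a pilot to be read through effect estimates and 95% confidence intervals, and that non-significance will not be taken as lack of effect.

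The cost is rewording only. No extra enrolment is asked for and the analysis is unchanged; the stated power becomes less favourable.
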